### Data management

5.5

Data are captured using an electronic CRF (eCRF) designed with ORACLE Database 11 g. The system ensures secure data handling according to strict standard operating procedures (SOPs). Trained site personnel enter data directly into the eCRF, including serious AEs (SAEs), serious adverse reactions (SARs) and suspected unexpected serious adverse reactions (SUSARs), which are also recorded in a separate Pharmacovigilance (PV) database. Monitoring visits and results are documented in a Monitoring Database. Data storage and backups follow strict SOPs, with central management ensuring data validation, medical coding and query resolution. Final database closure involves comprehensive checks and approvals to ensure data integrity.

### Data analysis

5.6

Summary statistics of overall participant retention within the trial until the 2‐year follow‐up visit will be presented. Full details of the analysis of all endpoints in the statistical analysis plan (SAP) will be provided, which will be finalised prior to any review or analysis of data.

*Analysis of participant populations*: The full analysis set (FAS) population and the safety set population will include all participants enrolled in the trial who received study treatment. Efficacy and safety analyses will be performed on these populations, respectively.

*HRQOL*: Summary statistics will be presented for items of each questionnaire by time point. Methods for scoring will follow the guidelines provided in the respective manuals. Further details on comparisons of questionnaires between time points and between arms will be provided in the SAP.

*PFS and OS*: The Kaplan–Meier (K‐M) methodology will be used to estimate the PFS and OS rates at 2 years, as well as the median PFS and OS for each treatment arm and for all participants. These estimates will be accompanied by 95% confidence intervals (CIs), and the K‐M curves will be plotted. The treatment effect will be evaluated by calculating the hazard ratio (HR) along with its corresponding CIs and p‐value, obtained from the Cox proportional hazards model.

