**Patients and Methods:**

Thirty participants with good prognosis stage II seminoma or NSGCTs will be recruited over 18 months into two cohorts: de‐escalation arm and SOC arm. The de‐escalation cohort will receive either Carboplatin AUC10 or robotic RPLND with or without adjuvant therapy depending on institutional SOC. Participants who decline or are ineligible for de‐escalation will receive SOC treatment: combination chemotherapy or radiotherapy for seminoma and combination chemotherapy for NSGCT. All participants will be followed for two years post‐treatment or until withdrawal. Data collection includes recruitment and retention rates, disease status, surgical outcomes, adverse events and patient‐reported outcomes using validated questionnaire: EORTC QLQ‐TC26, EORTC QLQ‐C30, Brief Male Sexual Function Inventory (BMSFI) and additional enquiries on anejaculation.

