Within the good prognosis group, stage II seminoma shows the most favourable oncological outcomes with long‐term cure rates of exceeding 98%,^3^ leading to explorations of non‐SOC therapy de‐escalation to reduce treatment‐related toxicity and maintain oncological outcomes.^3^ A prospective multicentre study of a single cycle of neoadjuvant Carboplatin AUC7 with reduced field and dose of radiotherapy for stage IIA/B seminoma yielded 3‐year progression‐free survival (PFS) rate of 93.7% with minimal toxicity.^5^ In a multi‐centre cohort, three cycles of Carboplatin AUC10 monotherapy for stage II seminoma yielded a 2‐year PFS rate of 96.5% and a 3‐year cancer‐specific survival (CSS) rate of 100%^6^ with only myelosuppression being a major acute toxicity. A recent prospective clinical trial of RPLND without adjuvant chemotherapy in stage IIA/B seminoma showed a 31% recurrence rate over a mean of 26 months follow‐up.^7^ Another prospective trial of RPLND reported an 81% 2‐year recurrence free survival (RFS) and low toxicity in small volume stage IIA/B disease.^8^ Similarly, a prospective trial of nerve‐sparing RPLND for stage IIA/B seminoma showed a 10% recurrence rate at up to 9 months follow‐up.^9^ To reduce the recurrence risk, one group has adopted a single cycle of adjuvant Carboplatin AUC7 after minimally‐invasive robot‐assisted RPLND (rRPLND), which appears to have low toxicity and relapse rates.^10^

Despite high PFS rates, fewer toxicities and better quality of life outcomes, de‐escalated treatments are not yet widely adopted as SOC primarily due to a lack of comparative outcomes data derived from prospective randomised clinical trials and limited adoption of minimally invasive RPLND. Consequently, a recent UK survey highlighted significant geographical heterogeneity in SOC treatments for stage II seminoma, and only a third of centres have adopted a treatment de‐escalation regimen.^11^ TGCTs are a rare cancer and account for only approximately 1% of newly diagnosed malignant tumours,^12^ hence there are challenges in recruitment to randomised controlled trials (RCTs), including ethical concerns over randomisation without clear equipoise, and patient and clinician biases regarding SOC and de‐escalated options.

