### Secondary objectives and endpoints

3.2

1Health‐Related Quality of Life (HRQOL)
2Sexual Drive, Function and Satisfaction
3Progression‐Free Survival (PFS) and Overall Survival (OS)
PFS at 2 years is defined as the proportion of participants who do not experience disease progression or death from any cause within the 2‐year follow up period.OS at 2 years is defined as the proportion of participants who remain alive from any cause at the 2‐year follow up period.The study aims for these survival rates to remain consistent with SOC treatments (>95%).4. Safety and Treatment‐Related Complications
4Safety and Treatment‐Related Complications
The incidence, nature and severity of adverse events (AEs) will be documented according to the Common Terminology Criteria for Adverse Events (CTCAE) v5.0, from the time of informed consent until 6 weeks post‐surgery or 6 months post‐chemotherapy.Surgical complications will be classified using the Clavien‐Dindo scoring system, and additional safety assessments will include analysis of blood transfusion rates, ITU (Intensive Therapy Unit) admissions and dialysis requirements from patient records up to 6 months post‐rRPLND.

The study aims to evaluate changes in HRQOL before and after treatment(s). This will be assessed by measuring changes in domain scale scores and single‐item scores from the European Organisation for Research and Treatment of Cancer (EORTC) QLQ‐TC26 and EORTC QLQ‐C30 from baseline until the 2‐year follow up visit. 2. Sexual Drive, Function and Satisfaction

Another objective is to assess changes in sexual drive, function and overall satisfaction before and after treatment(s). This will be evaluated by tracking changes in domain scale scores and single‐item scores in the Brief Male Sexual Function Inventory (BMSFI), QLQ‐TC26 and supplementary anejaculation‐related questions, with assessments conducted from baseline to the 2‐year follow‐up visit.3. Progression‐Free Survival (PFS) and Overall Survival (OS)

The study also aims to evaluate PFS and OS rates to ensure they align with standard‐of‐care treatment outcomes.

The study seeks to assess the safety and complications associated with all treatments.

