### Intervention

5.1

Participants will receive SOC treatments for good prognosis stage II seminoma and NSGCT or de‐escalated treatments (primary rRPLND with or without adjuvant treatment or Carboplatin AUC10) for stage II seminoma. Participants will be allocated to one of the following two cohorts based on whether the relevant de‐escalated treatment is adopted as an institutional SOC:rRPLND cohort: Participants with ipsilateral stage IIA or <3 cm IIB seminoma with negative/low for tumour markers will be offered rRPLND followed by adjuvant treatment or surveillance based on post‐operative histology as per institutional SOC.Carboplatin AUC10 cohort: Participants with stage II seminoma will be offered Carboplatin AUC10 by 3 cycles.

Participants deemed ineligible for Carboplatin AUC10 or rRPLND or those who decline this de‐escalation option will be offered either BEP or EP chemotherapy (seminoma and NSGCT) or radiotherapy with or without neoadjuvant Carboplatin AUC7 (seminoma) and will continue to be followed in the study. Chemotherapy treatment strategies and adjuvant treatments are left to the shared decision‐making between treating clinicians and participants and follow institutional SOC. The study flow diagram outlining the treatment cohorts is summarised in Figure 1.

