### Sample size

5.2

This is a 30‐participant feasibility study across 2 cohorts with an 18‐month recruitment period. Hence, sample size calculation is not appropriate, but the recruitment target is typical for feasibility studies.^13^

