## DISCUSSION

12

There is a need for prospective trials to assess de‐escalation strategies for stage II seminoma, particularly to determine the efficacy, safety and toxicity of treatments. The lack of randomised trials in this area has led to varied institutional SOC, shaped by individual clinical experiences, making it difficult to reach an international consensus on treatment strategies.

THERATEST is the first study to prospectively evaluate standard of care treatments (multi‐cycle combination chemotherapy or external beam radiotherapy) and novel de‐escalation strategies (Carboplatin AUC10 and rRPLND with or without adjuvant chemotherapy) for good prognosis GCT. This study will contribute valuable insights to the literature by combining qualitative and quantitative data to comprehensively assess outcomes. The study will not only enhance our understanding of clinical efficacy but also provide a deeper insight into the patient‐reported outcomes, which is crucial for optimising treatment decisions within a shared decision‐making framework.

However, the study has several limitations. The relatively short follow‐up period of 2 years may be insufficient to fully assess long‐term disease relapse and treatment‐related effects. Additionally, the generalisability of the findings may be limited, as all rRPLND procedures will be performed by a small team of surgeons at a single centre. Furthermore, the lack of randomisation in treatment allocation restricts the study's ability to evaluate the feasibility of incorporating randomisation in future trials.

If successful in achieving its primary outcomes of recruitment and retention, THERATEST will lay the groundwork for a larger‐scale multicentre study, with the potential to inform broader evidence and shape future clinical guidelines. The study's findings will be crucial in addressing existing gaps in evidence and shaping the direction of future research on de‐escalation strategies for this rare cancer.

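### Section 5.6 commits to a Cox hazard ratio and p-value as the treatment effect on PFS and OS, but 30 non-randomised participants with very few events cannot support either

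*Protocol article*

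**What the plan says.** Section 5.6 (Data analysis) plans Kaplan–Meier 2-year rates, medians and curves for PFS and OS, by treatment arm and overall, with 95% CIs. It then adds: "The treatment effect will be evaluated by calculating the hazard ratio (HR) along with its corresponding CIs", together with a p-value from a Cox proportional hazards model. The sentence carries no exploratory label, minimum event count or adjustment. The section leaves full analysis details to the SAP but does not make this comparison conditional on it.

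Other relevant statements in the protocol article:

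- Abstract, Patients and Methods: "Thirty participants with good prognosis stage II seminoma or NSGCTs will be recruited over 18 months into two cohorts". These are named there as a de-escalation arm and an SOC arm.
- Section 3.2: "The study aims for these survival rates to remain consistent with SOC treatments (>95" (a percentage, for PFS and OS at 2 years).
- Section 5.2: "sample size calculation is not appropriate, but the recruitment target is typical for feasibility studies".
- Section 2.2: at least 5 participants per de-escalation group, at most 15 in the SOC groups, and no replacement of withdrawals.
- Section 5.1: "Participants will be allocated to one of the following two cohorts". Here the two are rRPLND and Carboplatin AUC10, set by institutional practice. Those ineligible or declining receive SOC and stay in the study.
- Discussion: "all rRPLND procedures will be performed by a small team of surgeons at a single centre".

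**The concern.** A Cox model comparing two arms has a finite hazard ratio only if both arms have at least one event. With 30 participants and rates near the protocol's target, that condition will often fail. When it holds, the interval will be too wide to inform anyone.

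The second problem would remain with more events. De-escalation is open to seminoma only, so every NSGCT participant is in SOC, along with seminoma patients who were ineligible or declined. Institution decides which de-escalated option is offered, and rRPLND is confined to one centre. The arms therefore differ by institution, eligibility, patient choice and histology, and a handful of events cannot support adjustment.

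At stake is a number labelled a treatment effect in a field that, by the Background's own account, lacks comparative data. A null p-value could be read as equivalence and an extreme ratio as harm or benefit. Neither reading would be justified.

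**Working it through.** The plan has no calculation to reproduce: section 5.2 gives 30 without one, and no event count, alpha, power or target hazard ratio is stated for PFS or OS.

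**Inputs.** N = 30 (abstract, section 5.2). The 2-year rate is 95%, the floor of the aim in section 3.2. Carboplatin AUC10 2-year PFS is 96.5% (Background). For RPLND the Background cites 10% recurrence at up to 9 months, 81% 2-year recurrence-free survival, and 31% recurrence over a mean of 26 months without adjuvant chemotherapy.

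**Assumptions.** The contrast is de-escalation v SOC, split 15 v 15. All participants have full 2-year follow-up with no dropout, which favours the plan. OS is 98–99%. The cited RPLND figures are used as if they were 2-year PFS.

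**Expected events** = Σ n(1 − p). At 95%: 30 × 0.05 = 1.5. At 98% and 99%: 0.6 and 0.3.

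**Chance of no finite hazard ratio** = 1 − (1 − p^n₁)(1 − p^n₂).

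At 95%, 15 v 15: 0.95^15 = 0.463, so 1 − (0.537)² = 0.712. This splits into no events at all, 0.95^30 = 0.215, and events in one arm only, 2 × 0.463 × 0.537 = 0.497. A simulation of one million trials also gave 71.2%.

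| 2-year rate, both arms | Expected events | 15 v 15 | 20 v 10 | 25 v 5 |
|---|---|---|---|---|
| 95% | 1.50 | 71% | 74% | 84% |
| 96.5% | 1.05 | 83% | 85% | 90% |
| 98% | 0.60 | 93% | 94% | 96% |
| 99% | 0.30 | 98% | 98% | 99% |

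The equal split is the most favourable of those tried.

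**Sensitivity of PFS to the cited RPLND results.** Of 15 de-escalation participants, 5 to 10 have rRPLND and the rest have PFS 96.5%. The 15 SOC participants have PFS 95–98%.

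| rRPLND figure used | Expected events | No finite hazard ratio |
|---|---|---|
| 10% recurrence | 1.2–1.9 | 62–85% |
| 81% recurrence-free | 1.6–2.8 | 52–80% |
| 31% recurrence | 2.2–4.0 | 47–77% |

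The worst corner is 10 rRPLND participants at 69%, 5 Carboplatin at 96.5% and 15 SOC at 95%. Events: 3.1 + 0.175 + 0.75 = 4.0. Chance of no finite ratio: 1 − (1 − 0.69^10 × 0.965^5)(1 − 0.95^15) = 0.474.

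**Precision when the ratio is finite.** The approximate 95% CI factor either side is exp(1.96 √(1/d₁ + 1/d₂)). One event per arm gives 16.0, three v one gives 9.6, and two v two gives exp(1.96) = 7.1.

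**Power, for context.** At two-sided 0.05 (assumed), Schoenfeld's formula needs 66 events for 80% power at a hazard ratio of 2 or 0.5. Power is about 7% with 2 events and 10% with 4.

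**The p-value.** With k events, all in one of two equal arms, the score statistic is about (k/2)/√(k/4) = √k. Four such events give z = 2 and p of about 0.046, while the exact two-sided value is 2 × 0.5⁴ = 0.125. The p-value can be computed, but at these counts it depends heavily on the approximation.

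**The case against.** The strongest reply is that little hangs on this analysis. The primary endpoint is recruitment of 30 participants in 18 months, the Discussion ties a larger study to recruitment and retention, and section 5.6 already contains the right descriptive output. No stated decision or sample size uses the hazard ratio. All of that stands and limits the reach of the point, but it does not justify the sentence as written.

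Several stronger readings are tempting and are not supported:

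- *That the protocol expects rates above 95%.* Section 3.2 states an aim. The cited RPLND results are worse, so for PFS a non-finite ratio ranges from likely to about an even chance. For OS it is very likely under the assumed rates.
- *That section 5.2 disclaims hypothesis testing.* It says only that a sample size calculation does not apply. The absence of any power basis is an inference from that.
- *That nothing could be computed.* With events in one arm only, a score-test p-value exists. Only the no-event case, 21% at the 95% rate, leaves nothing to calculate.
- *That the contrast is wholly undefined.* The abstract names de-escalation and SOC arms. Section 5.1 uses cohort for rRPLND and Carboplatin AUC10 groupings that each include SOC patients. This is loose wording and a smaller point.
- *That the survival analysis must be replaced.* Kaplan–Meier handles censoring and should stay. Medians that are not reached do no harm.

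**Conclusion.** The concern holds. Section 5.6 fixes a hazard ratio, CI and p-value as the evaluation of treatment effect, and the design cannot deliver an interpretable one. At the protocol's 95% floor and an assumed 15 v 15 split, about 1.5 events are expected and there is a 71% chance of no finite ratio. For OS at an assumed 98–99% the chance is 93–98%. In the most pessimistic PFS scenario drawn from the Background, about 4 events are expected and the chance is still roughly half. That scenario is unlikely, because Table 1 lists adjuvant treatment for node-positive seminoma.

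The confounding argument does not depend on these rates: a finite ratio would still reflect institution, eligibility, choice and histology. The consequence is confined to a secondary endpoint.

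**What to change.** In section 5.6, delete the hazard ratio, its CI and the p-value. State that PFS and OS are descriptive, and report event counts and the already planned Kaplan–Meier 2-year estimates with 95% CIs by treatment received, showing seminoma and NSGCT separately within SOC. Restrict any between-group display to seminoma and label it exploratory and non-causal. State which groups the term treatment arm refers to, and carry the same wording into the SAP.

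The cost is wording only. Section 6 describes version 5.0 as final, so the change needs a deliberate amendment. No data collection, visit or sample size changes, and the only output lost is a comparison that could not be interpreted.

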## BACKGROUND

1

Standard of care (SOC) treatments for International Germ Cell Cancer Collaborative Group (IGCCCG) good prognosis metastatic testicular germ cell tumours (TGCT) include primary orchidectomy followed by combination chemotherapy (three cycles of Bleomycin, Etoposide and Cisplatin (BEP) or four cycles of Etoposide and Cisplatin (EP))^1^ with cure rates exceeding 95%.^2^ Alternatives are external beam radiotherapy (30–36 Gy in 2Gy fractions) for stage IIA/B seminoma, and primary retroperitoneal lymph node dissection (RPLND) for selected marker‐negative stage IIA/IIB non‐seminomatous germ cell tumour (NSGCT). However, combination chemotherapy is associated with early haematological and non‐haematological toxicities (reviewed in^3^) and radiotherapy can lead to late effects, including second malignancies, resulting in reduced utilisation in some centres.^4^ RPLND is typically an open surgical procedure with associated morbidity, and key long‐term side effect is ejaculatory dysfunction due to surgical damage to the lumbar sympathetic chain and pre‐aortic plexus.

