### Recruitment

2.2

Thirty evaluable participants with histologically confirmed good prognosis stage II seminoma and NSGCT who have not previously received chemotherapy or radiotherapy will be enrolled from UK sites. A minimum of 5 participants will be recruited into each treatment de‐escalation group within each cohort, and a maximum of 15 patients will be recruited into the SOC groups. In the event of withdrawal, participants will not be replaced in this feasibility study. Participants will be identified in the secondary care setting via supra‐regional multi‐disciplinary team (MDT) meetings at research sites.

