### Primary objective and endpoint

3.1

The primary objective of this study is to assess the feasibility of recruitment and retention by measuring the number of participants recruited per month and retained annually. The primary endpoint for this study is the successful recruitment of 30 participants into the THERATEST study within 18 months from the first participant enrolled.

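### The Cox hazard ratio fixed for PFS and OS will probably have no finite estimate at the protocol's own event rates, and will be nearly uninformative when it has one

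*Protocol article*

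**What the plan says.** Section 5.6 (Data analysis) of the protocol article plans Kaplan–Meier estimates of 2-year PFS and OS, per treatment arm and overall, with 95% CIs and curves. It then fixes the between-arm measure: "The treatment effect will be evaluated by calculating the hazard ratio (HR) along with its corresponding CIs", with a p-value, from a Cox proportional hazards model. The sentence covers both endpoints and contains no proviso about the number of events.

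The figures that determine how many events to expect are elsewhere in the article:

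- Section 3.1 sets the primary endpoint as "successful recruitment of 30 participants into the THERATEST study within 18 months from the first participant enrolled".
- Section 2.2 limits the comparator: "a maximum of 15 patients will be recruited into the SOC groups". For the de-escalation groups it says: "A minimum of 5 participants will be recruited into each treatment" de-escalation group.
- Section 3.2 gives the aim for 2-year PFS and OS: "The study aims for these survival rates to remain consistent with SOC treatments (>95"%).
- Section 5.2 says of the size of the study: "Hence, sample size calculation is not appropriate, but the recruitment target is typical for feasibility studies".

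**The concern.** A Cox model with a group indicator has a finite maximum-likelihood estimate only if each group has at least one event. If one arm has none, the likelihood keeps rising as the hazard ratio goes to zero or infinity. There is then no point estimate to report, and the usual standard error and interval cannot be used. If neither arm has an event, there is nothing to fit.

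The protocol expects very few events, so this is a likely outcome here. The named measure of treatment effect would then be missing. If the estimate did exist, it would rest on one or two events per arm, with an interval compatible with almost any effect. The study hopes to show survival in line with SOC, so a hazard ratio and p-value of that quality should not be prespecified as the way the treatment effect is judged.

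**Working it through.** The article states no event count, power or target hazard ratio, so there is no figure of the plan's own to reproduce. The check is whether the promised estimate can be expected to exist.

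**Inputs**

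- Total 30 (Section 3.1). SOC at most 15 (Section 2.2), so at least 15 de-escalated if 30 are reached. Base case: 15 v 15.
- 2-year PFS and OS above 95% (Section 3.2). Using exactly 95% is the least favourable value within that aim.
- OS of 98% is an assumption. The Background cites long-term cure above 98% for stage II seminoma but gives no 2-year OS.
- Sensitivity values from the Background: 2-year recurrence-free survival of 81% in one RPLND trial, and 2-year PFS of 96.5% with Carboplatin AUC10.
- Assumptions: the hazard ratio compares all de-escalated participants with all SOC participants (the article does not define the contrast), events are independent, and follow-up to 2 years is complete. Loss to follow-up would lower the event count.

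**Expected events at 95%:** 30 × 0.05 = 1.5. The chance of no event at all is 0.95^30 = 0.215.

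**Chance that at least one arm has no event**

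P = 1 − (1 − S1^n1)(1 − S2^n2)

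| Scenario | S1^n1 | S2^n2 | P |
|---|---|---|---|
| 95% v 95%, 15 v 15 | 0.463 | 0.463 | 1 − 0.537² = 0.712 |
| 95% v 95%, 20 de-escalated v 10 SOC | 0.358 | 0.599 | 0.743 |
| 98% v 98%, 15 v 15 (OS, assumed) | 0.739 | 0.739 | 1 − 0.261² = 0.932 |
| 81% v 95%, 15 v 15 (PFS, every de-escalated participant at the RPLND rate) | 0.042 | 0.463 | 1 − 0.958 × 0.537 = 0.486 |

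In the last row the expected number of events is 15 × 0.19 + 15 × 0.05 = 3.6.

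A mixed de-escalation arm lies between the extremes. With 5 to 10 rRPLND participants at 81%, the rest of the 15 on AUC10 at 96.5%, and 15 SOC at 95%, P is 0.59 to 0.52. With SOC at 98% instead, it is 0.80 to 0.77.

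**Precision when the estimate exists.** With one event in each arm the standard error of the log hazard ratio is about √(1/1 + 1/1) = 1.414. For a hazard ratio of 1 the 95% CI is exp(±1.96 × 1.414), or about 0.06 to 16. A direct Cox fit to a data set of 30 with one event per arm gave 0.06 to 16.6. With both events in the same arm, the fit failed with a singular matrix.

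**The case against.** Five points can be made for the plan.

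*The SAP will deal with it.* Section 5.6 defers full analysis details to a SAP that is not shown here, and rules for sparse events usually belong there. This stands to the extent that the absence of a fallback in the article is not a fault. The fault is the unconditional commitment. The same section leaves between-arm questionnaire comparisons to the SAP but fixes the Cox hazard ratio for PFS and OS itself.

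*The PFS event rate may be higher than the aim.* This stands in part. At the cited RPLND rate in all de-escalated participants, a finite PFS hazard ratio is about as likely as not. That case lies outside the protocol's own aim. It also ignores the AUC10 participants and the adjuvant treatment that Table 1 lists as typical for node-positive disease. It does not alter the OS result.

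*The p-value is not necessarily meaningless.* A reader might infer that the printed p-value will be close to 1, or that significance is practically impossible. The article does not support this, because it names no test. In simulation at 81% v 95%, 15 v 15, p fell below 0.05 in about 0.5% of studies by a Wald test, 16% by a score test and 27–28% by a likelihood-ratio test. The last two are defined when one arm is empty. The point here is the missing or very imprecise hazard ratio.

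*There is no contradiction with Section 5.2.* A reader might infer that declining a sample size calculation conflicts with reporting a treatment effect. It does not. The size of the study rests on feasibility, PFS and OS are secondary, an unpowered secondary comparison is permissible, and no significance level or decision rule is attached to it.

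*Kaplan–Meier rates with CIs are already planned.* This is correct, and a reader would see the sparse events in them. It also means that little is lost by dropping the hazard ratio.

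**Conclusion.** The concern holds as a point about estimability and precision. If the protocol's aim is met, the ordinary Cox hazard ratio has no finite value in about 71% or more of studies for PFS, and in about 93% for OS at an assumed 98%. The PFS figure falls to about 49% in the least favourable case, where every de-escalated participant has the cited 81% rate and SOC stays at 95%. One event per arm gives a CI of about 0.06 to 16.

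These figures rest on 15 v 15, a de-escalation v SOC contrast, independent events and complete 2-year follow-up. The aim is above 95%, so 71% is a lower bound under that aim for this split, and a 20 v 10 split gives 74%. The calculation says nothing about the comparability of the groups and leaves the primary recruitment and retention objective untouched. The change should be made, but it is of moderate weight because no stated decision depends on the hazard ratio.

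**What to change.** In Section 5.6, and to match in the SAP, replace the sentence on the Cox hazard ratio, its CI and p-value. Report the number of events and person-time per treatment group, descriptively, beside the 2-year Kaplan–Meier rates and CIs already planned.

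If a between-group contrast is wanted, use one of these:

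- the difference in 2-year event proportion with an exact or score interval;
- a Firth-penalised hazard ratio with a profile-likelihood interval.

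Either should be labelled exploratory and reported without a p-value, with a statement that no efficacy inference will be drawn.

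The cost is one sentence in each document and the loss of a conventional hazard ratio and p-value that would be inestimable or nearly uninformative. Recruitment, data collection and the primary endpoint do not change.
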